### Primary outcome

The primary outcome will be assessed by a planned comparison of the difference between groups in change of the primary outcome variable (EMITS) from T1 to T2. This test will be undertaken with an alpha of 0.05. An unstructured residual variance–covariance matrix will accommodate within-participant dependency. Tests of significance will use appropriate degrees of freedom adjustment where necessary (e.g., the Kenward-Roger method based on the observed information matrix). Where necessary, transformation of the outcome variable will be undertaken to ensure distributional assumptions of the model are met.

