### Procedure

#### Recruitment

The recruitment target has been set at 380 participants. This number will allow detection of a small-to-medium size effect (Cohen’s *d* = 0.4) with 90% power and alpha 0.05, conservatively assuming a correlation between pre- and post-training scores of 0.5. This sample size allows for up to 30% attrition at T2 (primary endpoint).

Participants will be recruited from a register of practitioners who have voluntarily signed up to receive the training program at https://meninmind.movember.com. The target sample size of 380 participants is considered feasible, given that this register currently contains in excess of 2000 registrations, and the pilot study succeeded in recruiting 67% of those approached. Assuming this rate of consent holds in the trial, a minimum of 567 individuals will be invited to take part (allowing for a non-response rate of 33%). Recruitment will be facilitated by the dissemination of an initial study link via email to a selection of registrants. In addition, the link to the study may be disseminated via social media advertisements and distribution among the personal and professional networks of the investigators, where necessary.

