### Statistical analysis

Analyses will be undertaken on an intention-to-treat basis and will include all participants in the group to which they were randomized (regardless of actual receipt or uptake of the intervention or withdrawal from the study). Mixed-model repeated measures analyses will be used because of the ability of this approach to include participants with missing data. The model will include factors of study condition (intervention or control group), occasion of measurement (T1, T2 and T3), and their interaction. Analyses will include the effect of the stratification variable, gender, with associated model parameters being retained if they are statistically significant.

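### Efficiency gain available at no cost: the primary model gives each arm its own T1 mean although T1 precedes randomisation, so the T1 to T2 contrast is less precise than it could be

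*Protocol article*

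**What the plan says.** The Statistical analysis section of the protocol article fixes the model: "The model will include factors of study condition (intervention or control group), occasion of measurement (T1, T2 and T3), and their interaction". The Primary outcome subsection then defines the test as a "planned comparison of the difference between groups in change of the primary outcome variable (EMITS) from T1 to T2" and adds: "An unstructured residual variance–covariance matrix will accommodate within-participant dependency". T1 EMITS is therefore one of the modelled responses. It is not named as a covariate, and nothing makes the T1 means equal across arms. The only covariate named is the stratification factor: "Analyses will include the effect of the stratification variable, gender, with associated model parameters being retained if they are statistically significant".

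The Design and Data collection sections place the T1 survey before randomisation. The Recruitment section sizes the trial at 380 for Cohen's d of 0.4, "with 90% power and alpha 0.05, conservatively assuming a correlation between pre- and post-training scores of 0.5", with room for 30% attrition at T2. The Secondary outcomes subsection applies the same methods to the confidence items and the DPCCQ and COSE subscales. It also asks for within-arm change from T1 to T3 and from T2 to T3.

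**The concern.** Randomisation guarantees that the arms have the same expected T1 mean. A model that nevertheless estimates a T1 mean for each arm, and subtracts it, brings the chance T1 difference into the treatment estimate at full weight. With complete data the condition by occasion contrast between T1 and T2 is exactly the difference in mean raw change. A contrast that uses the known equality of T1 means weights the chance T1 difference by the regression of T2 on T1 instead, and is more precise at any correlation below 1.

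At stake are the width of the confidence interval for the primary effect and the dependence of power on a correlation for which the document shows no observed value. The secondary scales inherit the same form. Their tests are to be adjusted for multiplicity, so precision matters there too.

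**Working it through.** **Inputs.** From Recruitment: d = 0.4, 90% power, alpha 0.05, correlation ρ = 0.5, 30% attrition at T2, N = 380. From Allocation: 1:1, so 190 randomised per arm and 0.7 × 190 = 133 with T2. Assumptions of this check: d is in raw-score SD units, SDs are equal at T1 and T2 (set to 1), the test is two-sided, T2 is missing at random, and T3 adds nothing. No observed ρ is given, so a range is shown.

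**1. The plan's own figure.** The variance of a change score is 2(1 − ρ), which is 1 at ρ = 0.5. The normal approximation gives n per arm = 2 × (1.960 + 1.282)² / 0.4² = 131.3, so 132. The t-based calculation gives 133. Then 2 × 133 / 0.7 = 380, which reproduces the target. A one-sided test would give about 309 and does not.

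**2. Variance formulas**, for the between-arm contrast with m = 133 completers of n = 190 per arm:
- change score in completers only: 2 × 2(1 − ρ)/m
- planned mixed model, free T1 means, T1-only participants included: 2 × [(1 − ρ²)/m + (1 − ρ)²/n]
- T1 means constrained equal: 2 × (1 − ρ²)/m
- T2 scores alone: 2/m

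Power = Φ(0.4/SE − 1.960).

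**3. Worked at ρ = 0.5.** Planned: 2 × (0.75/133 + 0.25/190) = 0.01391, SE 0.118, power 92.4%. Constrained: 2 × 0.75/133 = 0.01128, SE 0.106, power 96.5%. The variance ratio is 1.233, so the constrained variance is 1 − 1/1.233 = 19% lower. The planned interval is √1.233 = 1.11 times as wide.

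**4. Worked at ρ = 0.3.** Planned: 2 × (0.91/133 + 0.49/190) = 0.01884, SE 0.137, power 83.0%. Constrained: 2 × 0.91/133 = 0.01368, SE 0.117, power 92.8%. The ratio is 1.377, so the variance is 27% lower.

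**5. Across the range.**

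| ρ | Completer change | Planned mixed model | T1 means equal | Variance ratio, planned to constrained |
|---|---|---|---|---|
| 0.2 | 73.2% | 78.5% | 91.5% | 1.47 |
| 0.3 | 78.7% | 83.0% | 92.8% | 1.38 |
| 0.4 | 84.6% | 87.7% | 94.5% | 1.30 |
| 0.5 | 90.4% | 92.4% | 96.5% | 1.23 |
| 0.7 | 98.8% | 99.1% | 99.5% | 1.12 |

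T2 scores alone give 90.4% at every ρ.

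**6. Thresholds for the planned model.** It matches T2 alone when (1 − ρ)²/190 = ρ²/133, that is ρ = 1/(1 + √(190/133)) = 0.456. It reaches 90% power when (1 − ρ²)/133 + (1 − ρ)²/190 = (0.4/3.2415)²/2 = 0.00761, that is ρ of about 0.45.

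**7. Simulation check** (4,000 replicates, 30% of T2 missing at random). Standard errors for baseline-adjusted, planned mixed model and completer change were 0.106, 0.117 and 0.122 at ρ = 0.5, and 0.117, 0.137 and 0.145 at ρ = 0.3. The baseline-adjusted and mixed-model estimates both averaged 0.40, the true effect.

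**The case against.** The best defence is that nothing here is wrong. The planned contrast is unbiased under randomisation, the sample size matches it, and at the plan's own inputs power exceeds the target. All of that stands.

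It also rules out four stronger readings that a reader might infer.

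- *That the plan discards baseline data.* It does not. T1 is a response, and participants with T1 only contribute, which is the stated reason for the method: "Mixed-model repeated measures analyses will be used because of the ability of this approach to include participants with missing data". Baseline is used inefficiently. Nor is the analysis wholly unadjusted, since gender enters the model and stays if significant.
- *That 90% power needs ρ of at least 0.5, and that below 0.5 the plan does worse than ignoring T1.* Those thresholds belong to a completer-only change score, or to a trial with no missing T2. For the planned model at 30% attrition they are about 0.45 and 0.46. With less attrition, 90% power holds lower still: to about 0.41 at 24% attrition and about 0.33 at 10%.
- *That power falls to 79% at ρ = 0.3.* That is again the completer figure; the planned model has 83.0%.
- *That the protocol is wrong to write* "conservatively assuming a correlation between pre- and post-training scores of 0.5". Power rises with ρ, so a value set below the expected one is conservative. The documents give no observed correlation, so they cannot show the word to be wrong.

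One further objection stands against a particular remedy. Moving T1 to the right-hand side as a covariate would remove it as an outcome, and the within-arm T1 to T3 estimates under Secondary outcomes need it there.

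**Conclusion.** The point holds as a free improvement in efficiency. At 30% T2 attrition the planned model's variance is 23% above what the same data allow at ρ = 0.5 and 38% above at ρ = 0.3. Power is 92.4% against 96.5%, and 83.0% against 92.8%. At ρ = 0.7 or higher the gain in power is negligible, although the interval still narrows somewhat. The planned model misses its stated 90% power only if ρ is below about 0.45 with the full 30% attrition. With T1 means constrained equal, power at 133 completers per arm stays at 90% or more for any ρ from 0 upward, because 2(1 − ρ²)/133 never exceeds 2/133.

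The figures rest on d in raw SD units, equal SDs at T1 and T2, T2 missing at random, no contribution from T3, and the normal approximation. They do not show an error in the sample size or a bias in the test.

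**What to change.** In Statistical analysis and Primary outcome, keep the mixed model, the unstructured covariance and T1, T2 and T3 as responses. State that the T1 means are constrained to be equal across arms: occasion effects, plus condition effects at T2 and T3, with no condition effect at T1. The primary contrast is then the between-arm difference at T2. With equal T1 means this is the same quantity as the difference in T1 to T2 change, so the registered outcome and the estimand are unchanged.

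Use the same form for the between-arm T1 to T2 contrasts of the secondary scales. Keep the within-arm change estimates under Secondary outcomes as they are.

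The cost is a sentence or two of analysis wording, settled before unblinding and notified to the registry as a protocol amendment. It needs no new data and no more participants. Neither the target of 380 nor the description of the assumed correlation has to change.

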## Methods

### Design

The study design is a randomized controlled superiority trial with two parallel groups. Participating practitioners will be randomly allocated, on a 1:1 basis, to the intervention group (*Men in Mind* training) or a waitlist control group. Randomization will be stratified by practitioner gender with three stratum: male, female, and a third stratum encompassing non-binary or self-identified genders. The trial will be sponsored by Orygen, Centre for Youth Mental Health, The University of Melbourne. Participant recruitment and consent, research assessments, and intervention will be conducted entirely online.

This trial will involve three occasions of measurement. The first will occur prior to randomization (pre-training/Time 1/T1); the second will occur at the conclusion of the 6-week training/waitlist period (post-training/Time 2/T2), this is the primary endpoint; and the third will occur at the conclusion of the 12-week follow-up period for the intervention group, and at the conclusion of the 6-week training period for the control group (follow-up/Time 3/T3).

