### Allocation

Participants will be randomized in a 1:1 ratio to either the intervention group (*Men in Mind* training) or control group (6-week waitlist). Permuted block randomization will be performed, using variable sized blocks, with stratification by participant gender (three strata: male, female and non-binary/self-identified gender). The randomization schedule will be generated before recruitment by an investigator unconnected with the day-to-day running of the trial.

Randomization will be programmed by our data management subcontractor, Strategic Data. The allocation schedule will be created by the study statistician and transferred directly to Strategic Data, unseen by the researchers. The eligibility of any individual participant will be automatically assessed and determined prior to group allocation, such that allocation cannot influence the decision to include or exclude the participant.

Online questionnaire data collection will be undertaken by Strategic Data who will use a purpose-built online platform for the survey. They will generate unique URLs for each participant based on their email address, so that participant responses can be connected across all surveys. At the end of trial, Strategic Data will provide the questionnaire data to the researchers in de-identified, blinded format.

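### A single unstructured covariance matrix, if common to both arms, would mis-size the standard errors of the planned within-arm T2–T3 contrasts wherever the arms' covariances differ; estimate it by arm

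*Protocol article*

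**What the plan says.** The Statistical analysis section sets one mixed model for everyone: "The model will include factors of study condition (intervention or control group), occasion of measurement (T1, T2 and T3), and their interaction". The Primary outcome section adds: "An unstructured residual variance–covariance matrix will accommodate within-participant dependency". Neither says whether the matrix is common to both arms or estimated within each. The Secondary outcomes section carries the same methods over to the secondary variables.

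The occasions do not mean the same thing in the two arms. Under Design, T3 falls "at the conclusion of the 12-week follow-up period for the intervention group, and at the conclusion of the 6-week training period for the control group". Under Data collection, the intervention arm trains between T1 and T2, while the control arm waits and gets access on submitting T2.

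Secondary outcomes plans to estimate T2–T3 change within each arm and T1–T3 change. It also sets the control arm's T2–T3 change beside the intervention arm's T1–T2 change, as a quasi-replication of the primary result.

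Under Recruitment, the plan gives one correlation for all participants, "conservatively assuming a correlation between pre- and post-training scores of 0.5", and one overall T2 attrition allowance of 30%. No standard deviation, correlation or attrition rate is given by arm. Under Retention, access that depends on completing T2 is described as an incentive for the control arm only.

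**The concern.** A common matrix assumes that the same occasion label carries the same variance, and the same correlation with the other occasions, in both arms. In this crossed waitlist design that is doubtful:

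- T1–T2 spans training in the intervention arm and an untreated retest in the control arm. T2–T3 spans 12 weeks of follow-up in the first and training in the second.
- T3 is at about week 18 (6 + 12) in the intervention arm and about week 12 to 14 in the control arm (6 + 6, plus up to 2 weeks to submit T2).
- The Background reports that in the pilot female practitioners started lower and caught up after training, so training may change the spread of scores and their link to baseline. EMITS is also bounded, at 13 and 65.

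A between-arm comparison with equal numbers averages such differences out. A single-arm change does not: it takes the averaged error whatever its own variance is. The contrast most exposed to an error that is too small is the control arm's change over training, which is offered as supporting evidence for the main result.

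**Working it through.** **The plan's own figure.** "The recruitment target has been set at 380 participants", for d = 0.4 "with 90% power and alpha 0.05". With r = 0.5 the change-score SD is √(2(1 − 0.5)) = 1.0. Two-sided, n per arm = 2(1.960 + 1.282)²/0.4², which rounds up to 132. The t-based value is 133, so 266 in all, and 266/0.7 = 380. The target reproduces and nothing below alters it.

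**Within-arm contrasts.** Correlations by arm are not in the document, so those used here are assumptions. With unit SDs, Var(T2–T3 change) = 2(1 − ρ). With equal numbers, a common matrix uses the mean of the two arm variances. The ratio of model SE to true SE is √(pooled/own), and the rejection rate of a nominal 5% test is 2[1 − Φ(1.96 × ratio)].

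| Assumed ρ: no training / across training | Variance: control, intervention, pooled | Control ratio, rejection | Intervention ratio, rejection |
|---|---|---|---|
| 0.5 / 0.5 | 1.0, 1.0, 1.0 | 1.000, 5.0% | 1.000, 5.0% |
| 0.6 / 0.5 | 1.0, 0.8, 0.9 | 0.949, 6.3% | 1.061, 3.8% |
| 0.7 / 0.5 | 1.0, 0.6, 0.8 | 0.894, 8.0% | 1.155, 2.4% |
| 0.8 / 0.5 | 1.0, 0.4, 0.7 | 0.837, 10.1% | 1.323, 0.95% |

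**Check with a full three-occasion likelihood fit.** This used 190 per arm, 30% attrition in each arm unrelated to scores, and 1,500 replicates. Assumed control SDs were 1, 1, 0.8 with r12 = 0.7, r13 = 0.4, r23 = 0.4. Assumed intervention SDs were 1, 0.8, 0.85 with r12 = 0.4, r13 = 0.4, r23 = 0.7. The common matrix gave 9.6% for control T2–T3 (SE ratio 0.85) and 1.4% for intervention T2–T3 (1.29). Arm-specific matrices gave 5.2% and 4.9%.

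**Primary contrast, standard error.** For completers' T1–T2 change, true variance = V_I/n_I + V_C/n_C and model variance = V_pooled(1/n_I + 1/n_C).

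- *Equal attrition:* V_pooled = (V_I + V_C)/2, so the two expressions are equal. The ratio is 1.000 and the error rate 5.0%, whatever the variances.
- *Variances 1.0 (intervention) and 0.6 (control):* 5.4% at 35%/25% attrition and 5.9% at 40%/20%. With the variances reversed: 4.6% and 4.2%.
- *Variances 1.0 and 0.4, attrition 40%/10% (n = 114 and 171):* V_pooled = (114 × 1.0 + 171 × 0.4)/285 = 0.64. Model variance = 0.64(1/114 + 1/171) = 0.00936; true variance = 1/114 + 0.4/171 = 0.01111. The ratio is 0.918 and the error rate 7.2%. A likelihood simulation of T1 and T2 gave 7.1%, and 5.2% with separate matrices.
- *Three-occasion simulation at 40%/20%:* SE ratio 1.02 and error rate 4.5% (Monte Carlo error about 1.1 points), so no detectable inflation.

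**Primary contrast, bias.** When dropout depends on the T1 score, the likelihood in effect predicts a missing T2 from a slope pooled over both arms. With 30% attrition in each arm, correlations 0.5 and 0.8, and a log-odds slope of 0.5 for dropout on T1, the bias was about 0.045 SD and the error rate 7.4%. Under the three-occasion covariances above, the bias was about 0.07 SD and the error rate about 10%. Separate matrices removed the bias in both settings (error rates 4.9–5.9%).

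**The case against.** The strongest reply is that the article never says the matrix is common. Arm-specific estimation is a detail that a condensed article may leave to the analysis plan, and the sentence as written is compatible with it. This stands in part: the common matrix is inferred. But one matrix is named for one model, and an analyst following the text would ordinarily fit it that way.

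Second, every magnitude depends on covariances the document does not supply. This stands fully; with equal covariances there is no error.

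Third, the affected contrasts are secondary and non-randomised, and the article already qualifies the quasi-replication for attrition and drift. That limits the consequences. However, those qualifications concern bias, not a mis-sized standard error. Nor are all within-arm contrasts hit: intervention T1–T3 had an SE ratio of 1.03 (error rate 4.2%) in the simulation.

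A reader might go further and infer that the primary test is itself mis-sized. The document does not support that. The standard error is right at equal attrition unrelated to scores. The 7.2% needs both 40% against 10% attrition and a 2.5:1 variance ratio. The direction reverses if the control arm is the more variable. The T2 incentive makes some imbalance foreseeable, but no rates by arm are given, and the Discussion expects little attrition between T1 and T2. A reader might also infer that missing intervention T2 values would be predicted from control-arm correlations; they would come from correlations pooled over both arms.

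**Conclusion.** The point holds conditionally. If the matrix is common to both arms, as the wording is usually read, and the arms' covariances differ, as the design makes plausible, then the within-arm T2–T3 standard errors are wrong even with equal numbers. The control arm's is too small and the intervention arm's too large when training lowers the retest correlation. Over the assumed range of 0.6 to 0.8 without training against 0.5 across it, the nominal 5% tests reject 6.3% to 10.1% of the time in the control arm and 3.8% to 0.95% in the intervention arm.

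The primary contrast is a secondary concern. At moderate attrition imbalance its error rate is about 4–6%, in either direction. Its estimate could be off by a few hundredths of an SD if dropout depends on T1 and the T1–T2 slopes differ by arm, and that bias does not need unequal attrition. This is an inexpensive improvement to the specification. It is not an error in the sample size, nor a demonstrated fault in the primary test.

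**What to change.** State under Primary outcome that the unstructured residual covariance matrix is estimated separately by arm, with Kenward-Roger or Satterthwaite degrees of freedom to match. Apply this in every model that includes T3 and in the primary test. If the analysis plan already says so, a sentence in the protocol confirming it is enough. Settle it before unblinding.

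The cost is six more covariance parameters (a three-occasion matrix has six, so twelve instead of six), which about 130 to 190 participants per arm can readily support. If the covariances are in fact equal, the loss of precision is negligible: in the equal-covariance simulation at 40%/20% attrition, the mean primary SE was 0.0935 with a common matrix and 0.0934 with separate ones. The target of 380 stays.

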### Secondary outcomes

Analyses of secondary outcome variables (Confidence items, DPCCQ and COSE subscales) will follow the same methods as the primary outcome. These analyses will be subject to appropriate adjustment for multiple testing. Secondary outcomes will also include change in the primary and other outcome variables from baseline (T1) to follow-up (T3) to inform the outcome pertaining to retention of learning. (Note that change in the intervention group over this period cannot be compared to the waitlist as the latter group will be provided with access to the intervention after T2.) The magnitude of change within both active and control groups from T2 to T3 will be also estimated to reflect retention of learning. T3 outcomes in the waitlist group will be compared to their T2 scores in order to estimate change in this group after they have accessed the training program. The extent of change will be contrasted to T1–T2 change attributable to the training program in the intervention group. Subject to qualifications arising due to attrition and natural drift over time, these analyses will stand as a quasi-replication of the primary outcome of the trial.

### Exploratory analyses

#### Examining the EMITS as a 17-item scale

The four items assessing confidence to engage male clients will be examined alongside the 13-item EMITS scale, to ascertain the reliability and validity of the scale as a 17-item measure to inform usage in future studies.

